# Effectiveness of a short-term multimodal prehabilitation program in adult patients awaiting selective cardiac surgery: study protocol for an open-label, pilot, randomized controlled trial

**DOI:** 10.3389/fcvm.2023.1201737

**Published:** 2023-06-30

**Keywords:** prehabilitation, cardiac surgery, exercise, nutrition, mindfulness

## Abstract

**Background:**

Prehabilitation has been demonstrated to positively impact postoperative recovery in patients undergoing selective cardiac surgery. However, the optimal modules included in prehabilitation programs are yet to be fully explored, as existing studies have primarily focused on exercise. This study will explore the effectiveness of a three-arm prehabilitation program among adult patients awaiting selective cardiac surgery.

**Methods and analysis:**

A single-center, parallel-group randomized controlled trial will be conducted at the Second Affiliated Hospital of Zhejiang University School of Medicine (SAHZU). A total of 152 adult patients scheduled for elective cardiac surgery (coronary artery bypass grafting or valvular surgery) will be recruited from a tertiary teaching hospital. The patients will be randomly assigned to either the control group or the prehabilitation group. Patients assigned to the control group will receive standard care, which includes patient education and counseling as well as personal guidance on exercise, breathing, and coughing. Patients in the intervention group will be provided a multimodal prehabilitation program, including nutrition guidance, a diet journal, mindfulness training, and exercise guidance. The interventions will begin with home-based training and continue after hospital admission and before surgery. The primary outcome will be the perioperative 6-minute walk distance (6 MWD). The secondary outcomes will include preoperative readiness, postoperative recovery, and patient experience with the program.

**Discussion:**

The purpose of the study is to examine whether a short-term multimodal prehabilitation program will be associated with improved preoperative readiness and postoperative outcomes. The findings of this study will provide evidence to support the development of a perioperative program aimed at enhancing patient recovery.

**Clinical Trial Registration:**

www.ClinicalTrials.gov; identifier: NCT05503004.

## Introduction

1.

Valve surgery and coronary artery bypass grafting (CABG) are the most common types of cardiac surgery in China, accounting for 49.2% of all heart surgeries performed in 2021 (1). However, these surgeries can potentially lead to cognitive and functional decline (2, 3), resulting in reduced independence and a diminished health-related quality of life (HRQOL) (4). Therefore, it is of paramount importance to enhance the physical and psychological reserve of patients in order to improve their readiness for surgical stress, ultimately promoting patient recovery.

Prehabilitation refers to the process of enhancing an individual's functional capacity in preparation for upcoming surgery (5). The current guidelines of the Enhanced Recovery Association recommend that prehabilitation should be incorporated into perioperative care for cardiac surgery (6). As the first step in the enhanced recovery process, prehabilitation can mitigate sympathetic nervous overreaction and enhance patients' physical and psychological resilience (7, 8). Although studies have indicated that multimodal, multidisciplinary preoperative interventions are more effective than single-exercise interventions (9), the content of preoperative interventions prior to cardiac surgery has been primarily limited to exercises, such as respiratory muscle training and aerobic training (10). Another important consideration is the duration of prehabilitation, which has ranged from five days to ten weeks (11). Additionally, the suitability and scheduling of prehabilitation programs could significantly affect patient participation and adherence (12). Given the shortened waiting duration before hospital admission, there is a need for a short-term prehabilitation program to enhance preoperative recovery.

Recent research has provided evidence indicating the importance of preoperative nutritional evaluations and psychological interventions. It has been observed that between 12%–42% of patients undergoing cardiac surgery suffer from malnutrition before surgery, which can increase the inflammatory response and negatively impact postoperative recovery (13). Several standardized scoring systems have been developed to assess the preoperative nutritional status of patients (14), but routine risk screening for malnutrition is not currently incorporated into prehabilitation programs, and optimal methods for providing preoperative guidance are overlooked. In addition to physical and nutritional status, psychological distress can also initiate a stress response prior to surgery and dysregulate postoperative immune function, leading to worse outcomes (15). Mindfulness-based interventions have been found to have favorable effects on psychological outcomes. A study conducted on patients with heart disease found that mindfulness can decrease heart rate and improve exercise capacity (16). Furthermore, evidence indicates that mindfulness-based intervention can reduce preoperative emotional distress and lead to less emotional pain perception after surgery (17). Therefore, mindfulness may be a valuable addition to prehabilitation program, and further research exploring the use of mindfulness in this context is needed.

Additionally, it is important to note that the three prehabilitation modules – exercise, nutrition, and psychological support – can also have an interdependent relationship. Qualitative interviews with patients who underwent elective cardiac surgery revealed that physical factors such as reduced mobility and weakness can easily lead to negative emotions in patients, which may hinder their participation in rehabilitation programs (18). Psychological distress and malnutrition have also been identified as potential barriers to participation in rehabilitation (19). Conversely, exercise has been shown to improve emotional distress such as anxiety and depression in patients with heart disease by reducing stress and behavioral activation (20). This suggests that the modules in prehabilitation programs can interact with each other and may have a synergistic effect.

Therefore, the aim of this study is to implement a short-term multimodal prehabilitation program and investigate the effectiveness of such a program in improving physical function in patients receiving selective cardiac surgery. Additionally, secondary outcomes will be assessed, including preoperative readiness (preoperative anxiety, frailty, and preoperative nutritional risks), postoperative recovery (delirium, frailty, HRQOL, and length of stay), and patient experience with the program.

## Methods

2.

### Trial design

2.1.

This study is a single-center, prospective, parallel group, randomized clinical trial with an allocation ratio of 1:1, comparing a one-week prehabilitation program to usual care at the Second Affiliated Hospital of Zhejiang University (SAHZU), located in Hangzhou, China. The overall trial design is illustrated in Figure 1. The trial protocol was developed following the Standard Protocol Items: Recommendations for Interventional Trials (SPIRIT) guidelines (21) and was pre-registered at clinicaltrials.gov (NCT05503004).

**Figure 1 F1:**
[figure not shown]
Study flowchart.

### Study setting

2.2.

This trial will be conducted at a tertiary academic hospital in Hangzhou, China (SAHZU). Patients will be assessed for eligibility at their initial visit to the cardiovascular clinic after receiving a clinical diagnosis requiring selective open-heart surgery. The one-week interventions will be performed at the patient's home while awaiting hospital admission and after hospital admission before surgery.

### Eligibility criteria

2.3.

Patients will be eligible for participation if they are 18 years or older and are referred for selective cardiac surgery with an expected waiting time of 7 days prior to the surgical procedure. The exclusion criteria will be as follows: (1) comorbid medical, physical, and mental conditions that contraindicated exercise or mindfulness; (2) acute or unstable cardiac conditions (e.g., unstable angina or symptomatic severe aortic stenosis); (3) disabling orthopedic and neuromuscular disease; hearing disorder; (4) dementia; (5) cardiac failure (New York Heart Association functional classes III and IV); (6) hospitalization or mechanical ventilation in the past 30 days; and (7) previous history of cardiac surgery. Patients will be withdrawn from the trial if: (1) they request to do so without any reasons; (2) they develop adverse events due to prehabilitation (e.g., fall); (3) they are referred to the transcatheter cardiac surgery after hospital admission.

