#### Control group

2.4.2.

Patients assigned to the control group will not receive any additional prehabilitation intervention. Instead, they will receive usual care, which will include a thorough admission assessment, education on inspiratory muscle training, breath exercises, coughing, online health education, counselling, and nutrition risk assessment.

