### Outcomes

2.5.

The timeline for this study will be one week. Prehabilitation will be implemented one week before the surgery, and the follow-up period will comprise of the perioperative period until the patient's discharge from the hospital. The outcomes will be assessed at four different time points: before the intervention (T0), upon admission to the hospital (T1), before surgery (T2), and after surgery (T3, before hospital discharge). Table 1 shows the complete assessment timeline.

**Table 1 T1:** Overview of assessment.

Measurement	T0: baseline	T1: hospital admission	T2: 1 day before surgery	T3: after surgery (before hospital discharge)
6-minute walk distance (6MWD)	×	×	×	×
Preoperative anxiety (APAIS)	×	×	×	
Frailty (FFPC)	×		×	×
Nutrition risks (NRS2002)	×	×		
Prehabilitation experience (FSS)		×	×	
ICU delirium (CAM-ICU-7)				×
Postoperative delirium (4AT)				×
Health-related quality of life (EQ-5D-5l)	×	×	×	×
Length of ICU stay, days				×
Length of hospital stay, days				×
Length of mechanical ventilation, hours				×

**The primary outcome** was the change in functional capacity over time, measured as the difference in absolute change in 6-minute walk distance (6 MWD) between T0 and T2 (primary analysis), as well as between T0 and T3. In this regard, a change of 20 meters from the baseline was deemed significant, indicating either an improvement or deterioration. To conduct this evaluation, participants will be instructed to wear comfortable footwear and walk back and forth in a 20-meter stretch of hallway for 6 min, aiming to reach a point of exhaustion by the end of the exercise. The tests will be conducted under the supervision of a blinded assessor following a standardized procedure to minimize potential sources of error due to bias or different levels of encouragement.

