### Randomization and blinding

2.7.

Eligible patients will have an equal opportunity to be randomly assigned to either the prehabilitation group or the control group in a 1:1 ratio. Randomization will be performed via a computer-generated block scheme and the resulting group assignments will be placed in opaque envelopes with sequential numbering by an independent research assistant not involved in this study. The research assistant will open a concealed envelope to allocate patients to their respective group. The main interventionist, assessor, and statistician will remain unaware of the group assignments until the envelope is sealed. Due to the intervention's inherent nature, it will not be possible to mask the participants or healthcare professionals.

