### Statistical analysis

2.10.

To compare baseline characteristics between groups, we will use an independent-samples t-test for continuous variables and a *χ*^2^ Test for categorical variables. To analyze differences in primary outcomes, we will use repeated-measures analysis of variance. All statistical analyses will be conducted using SPSS (version 27.0; IBM) and R (version 4.0.5).

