This study will implement a comprehensive prehabilitation program that will be both home- and hospital-based, covering the entire waiting period before surgery. Our proposed prehabilitation program is designed to optimize preoperative and postoperative physical function performance and improve psychological well-being by enhancing physical function and alleviating psychological distress. This program was designed and will be supervised by physiotherapists, psychologists, nutritionists, cardiac rehabilitation nurse specialists, and cardiac surgical physicians, and the intensity of the program will be tailored to each patient's needs to ensure safety and effectiveness both practiced at home and in hospital. If this program is proven effective, it could provide significant benefits to patients on the waiting list by offering home-based prehabilitation and continuing care programs after hospital admission and postoperative recovery.

This study has some limitations. First, the study only includes patients awaiting for CABG and/or valve surgery. Second, this is a single-center study. Therefore, further multicenter studies including more patients with various diagnoses are needed. Third, due to the time window of 7 days, although the nutritional intervention may be beneficial for postoperative recovery, measurable changes in body composition or serum albumin concentrations may not be detectable.

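### Section 2.3 withdraws from the trial any patient with an adverse event due to prehabilitation; only one arm can meet this rule, so randomisation no longer protects the 6MWD comparisons

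*Protocol article*

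**What the plan says.** Section 2.3 (Eligibility criteria) ends with three reasons for removal, introduced by "Patients will be withdrawn from the trial if". The first is the patient's own request. The second is "2) they develop adverse events due to prehabilitation (e.g., fall". The third is referral for a transcatheter procedure after admission. The removal is from the trial, not just from the programme.

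Section 2.4.2 says of the comparator: "Patients assigned to the control group will not receive any additional prehabilitation intervention".

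Section 2.5 defines the primary outcome through the change in 6MWD, "measured as the difference in absolute change in 6-minute walk distance (6 MWD) between T0 and T2 (primary analysis", with the T0 to T3 change alongside it. T2 is one day before surgery and T3 is before discharge. Section 2.10 says: "To analyze differences in primary outcomes, we will use repeated-measures analysis of variance". Nothing in the article says that a patient withdrawn under the second reason is still measured at T2 or T3, or is analysed in the assigned arm.

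**The concern.** A randomised comparison is protected only while staying in the data does not depend on what the assigned treatment did to the patient. This rule makes it depend on exactly that. A prehabilitation patient whose fall is put down to the programme leaves the trial, while a control who falls in the same week stays. What remains of the prehabilitation arm is selected for having tolerated the programme, and no matching selection is made among controls.

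The timing makes this matter for the primary analysis. The programme runs from entry on the waiting list until surgery, so nearly all such events come before the T2 walk. Repeated-measures ANOVA in its usual form uses only patients with every measurement, so a patient withdrawn before T2 drops out of the primary comparison. The T0-T3 comparison is exposed in the same way.

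**Working it through.** **Which arm can meet each reason**

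| Reason in section 2.3 | Prehabilitation arm | Control arm |
|---|---|---|
| Patient's request | possible | possible |
| Adverse event due to prehabilitation | possible | not possible (section 2.4.2) |
| Transcatheter referral | possible | possible |

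Only the second reason is confined to one arm by its own definition.

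**The plan's own figures**

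Section 2.9 gives a 20 m target difference, 132 patients before attrition, 15% attrition, and 152 in total (76 per arm). The 132 is reproduced by a between-groups repeated-measures ANOVA with two groups and four measurements, alpha 0.05, effect size f = 0.25 and correlation 0.5 (power 0.9501); f and the correlation are assumed, because the article states neither. The step to 152 is 132 x 1.15 = 151.8. These figures neither support nor weaken the point. The 20 m and the 76 serve only to scale it.

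**Formula for the bias**

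Let p be the share of the prehabilitation arm removed under the rule. Let m be the mean 6MWD change among those who remain, and let the removed patients' mean change be d metres lower.

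- Mean of the whole arm as randomised: (1 - p) x m + p x (m - d) = m - p x d
- Mean actually analysed: m
- Excess: p x d

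The rule removes no controls, so nothing offsets this and the treatment difference is too large by p x d whenever d is above zero.

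**Numbers**

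The article gives no adverse event rate and no walk distances for such patients, so p and d are assumptions shown over a range.

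| p | Patients (p x 76) | d | Bias p x d | Share of 20 m |
|---|---|---|---|---|
| 1% | 0.8 | 20 m | 0.2 m | 1% |
| 2% | 1.5 | 40 m | 0.8 m | 4% |
| 5% | 3.8 | 60 m | 3 m | 15% |
| 10% | 7.6 | 60 m | 6 m | 30% |
| 10% | 7.6 | 100 m | 10 m | 50% |

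The last row is an extreme case. The plan allows 15% attrition from all causes, which is 0.15 x 76 = 11.4 patients per arm, and p = 10% would give 7.6 / 11.4, or two thirds, of that to this one cause.

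**The case against.** The strongest reply is that the bias may be trivial. The programme lasts a week and its exercise is of limited, monitored intensity. Section 2.3 already excludes patients with contraindications to exercise, unstable cardiac disease, NYHA class III or IV failure, and disabling orthopaedic or neuromuscular disease. The Discussion says that intensity is tailored "to ensure safety and effectiveness both practiced at home and in hospital". If events are rare and mild, the bias is about 1 m or less. That stands, and it is why the range starts there. It limits the size but does not make the rule sound.

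A second reply is that a fuller protocol or an SAP may define an intention-to-treat set. It may, but an analysis set cannot restore T2 and T3 walks that were not done because the patient had been withdrawn. The wording of section 2.3 is what has to change.

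A third reply is that retaining these patients recovers less than p x d, because the worst affected may be unable to walk at T2. That is correct, and the fix has to provide for it.

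Some stronger readings are tempting but not supported:

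- **Harms vanish from the data.** The article does not say that events go unrecorded or that data are deleted. An event has to be identified to trigger the rule, and section 2.8 documents daily feedback during the programme.
- **Unmasked staff decide who is removed.** Section 2.7 says "it will not be possible to mask the participants or healthcare professionals", but the article does not say who attributes an event to prehabilitation. Knowledge of the arm may well enter that judgement, but this is inference.
- **Delirium and length of stay are biased too.** ICU stay and postoperative recovery come from electronic records, and the article does not say that these stop being used after withdrawal.
- **The false-positive rate is inflated to a given percentage.** The article gives no SD for the 6MWD change, and a simple two-group test of that change is not the planned ANOVA. No error rate can be derived from what is printed.

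**Conclusion.** The point holds as a defect in the wording of section 2.3. A removal rule that only one arm can meet, triggered by a consequence of the assigned treatment, takes away the protection of randomisation for the T0-T2 and T0-T3 6MWD comparisons. This follows from the text and needs no assumption about numbers.

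A reader might go further and conclude that the effect is certainly biased upward. The document does not establish that. The direction rests on one premise that is natural but unstated: that patients harmed by the programme, for example by a fall, would walk less far than the rest of their arm. The size rests on p and d, which are not given. Under assumed values it runs from 1 m or less, through 3 m, to 10 m in an extreme case, against the 20 m target.

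**What to change.** In section 2.3:

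- Remove the second reason from the list of reasons for withdrawal from the trial.
- State that stopping programme components after an adverse event is a treatment decision left to the clinical team, and is not withdrawal from follow-up.
- Assess these patients at the existing T2 and T3 visits where they are able, and analyse them in their assigned arm.

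For the patients the visits cannot recover, report by arm the number unable to walk at T2 and T3, and add a sensitivity analysis for their missing values. Record adverse events in the same way in both arms, so that a fall in a control counts as a fall in a prehabilitation patient does.

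The cost is a sentence or two in section 2.3 and a short addition to the analysis. The visits already exist and the stated sample size does not change. The one downside is a slightly smaller expected effect, because patients who did not tolerate the programme stay in the comparison.

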### Sample size

2.9.

We determined that a difference of 20 meters in the change in 6-minute walk distance (6 MWD) between T0 and the T2 (primary analysis) in the prehabilitation group compared to the control group was a meaningful clinical outcome based on a previous study (22). Consequently, we conducted a sample size calculation using G*Power (version 3.1.) for the repeated-measures ANOVA with an alpha error of 5% and power of 0.95, with two groups and four measurements. The estimated sample size required was 132 patients. To account for a 15% attrition rate during the intervention period, the target sample size was increased to 152 participants (76 per group).

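### Section 2.3 withdraws patients from the trial, not only from the programme, for adverse events due to prehabilitation, a rule that only the prehabilitation arm can meet

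*Protocol article*

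**What the plan says.** Section 2.3 (Eligibility criteria) closes with three post-enrolment rules, introduced by "Patients will be withdrawn from the trial if". Rule (1) is the patient's own request. Rule (2) is that "they develop adverse events due to prehabilitation (e.g., fall" is given as the example. Rule (3) is that "they are referred to the transcatheter cardiac surgery after hospital admission". In all three the stated consequence is leaving the trial. Stopping the intervention is not mentioned as a separate step.

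The design is a "randomized clinical trial with an allocation ratio of 1:1". On the comparator, section 2.4.2 states: "Patients assigned to the control group will not receive any additional prehabilitation intervention".

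Section 2.5 defines the primary outcome as "the difference in absolute change in 6-minute walk distance (6 MWD) between T0 and T2 (primary analysis"), with T0 to T3 also assessed. Section 2.9 takes as clinically meaningful "a difference of 20 meters in the change in 6-minute walk distance (6 MWD) between T0 and the T2" and enlarges the sample from 132 to 152 with the words "To account for a 15% attrition rate during the intervention period". Section 2.10 names repeated-measures analysis of variance. The article does not say that a patient withdrawn under rule (2) is still assessed at T1, T2 or T3.

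**The concern.** Rule (2) operates after randomisation, and its trigger is defined by the assigned treatment. A control patient who falls at home stays in the trial. A prehabilitation patient whose fall is attributed to the programme leaves it. The attribution is a judgement, the article does not say who makes it, and section 2.7 accepts that healthcare professionals cannot be masked.

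A fall, the article's own example, plausibly reduces walking distance. If so, the prehabilitation patients who remain are selected for having tolerated the programme, while the control arm undergoes no matching selection. That would tend to favour prehabilitation on 6-minute walk distance and on other outcomes that need an assessment, such as frailty and EQ-5D-5L. A larger sample does not remove such a bias. An analysis set defined elsewhere cannot recover T2 or T3 walks that were never done.

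**Working it through.** **1. The plan's own figure.** The concern does not rest on the sample size, but the calculation supplies the arm size and the target. Section 2.9 gives alpha 0.05, power 0.95, two groups and four measurements. It states neither effect size nor correlation. Assuming f = 0.25, a correlation of 0.5 and the between-groups test:

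- noncentrality = f² × N × m / (1 + (m − 1) × ρ) = 0.0625 × 132 × 4 / 2.5 = 13.2
- power at N = 132 is 0.9501, and 132 is the smallest even N that reaches 0.95

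The stated 132 is reproduced. Then 132 × 1.15 = 151.8, giving the stated 152, or 76 per arm. The margin is 76 − 66 = 10 patients per arm.

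**2. Is the rule one-sided?** Setting the sections side by side:

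| Rule in 2.3 | Prehabilitation arm | Control arm |
|---|---|---|
| (1) patient request | possible | possible |
| (2) adverse event due to prehabilitation | possible | not possible, as no prehabilitation is given (2.4.2) |
| (3) transcatheter referral after admission | possible | possible |

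Only rule (2) depends on arm by construction.

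**3. Size of the bias.** Let q be the share of the prehabilitation arm removed and D the number of metres by which their mean T0–T2 change would be worse than that of the rest of the arm. If those retained have mean R, the whole arm has mean (1 − q) × R + q × (R − D) = R − q × D. Analysing only those retained overstates the arm mean, and so the arm difference, by q × D. The article gives neither q nor D, so both are assumptions.

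| q | Patients of 76 | D = 50 m | D = 100 m | Share of 20 m |
|---|---|---|---|---|
| 1% | 0.8 | 0.5 m | 1 m | 2.5–5% |
| 5% | 3.8 | 2.5 m | 5 m | 12.5–25% |
| 10% | 7.6 | 5 m | 10 m | 25–50% |

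All three removal rates fit inside the margin of 10 patients per arm.

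**4. Effect on false positives.** Suppose there is no true difference between the arms as randomised, and the T0–T2 changes are compared by a two-sided 5% normal test. The standard error is SD × √(1/76 + 1/(76 × (1 − q))), and the test is shifted by q × D divided by it. The article gives no SD of change, so 32 to 60 m is assumed. The lower end is the SD at which 66 per arm gives 95% power for 20 m: 20 / (√(2/66) × (1.960 + 1.645)) = 31.9 m.

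| q | Type I error over D = 50–100 m and SD = 32–60 m |
|---|---|
| 1% | about 0.050–0.054 |
| 5% | about 0.06–0.16 |
| 10% | about 0.08–0.47 |

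With rare events the effect is negligible. If several patients are removed it can be material.

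**The case against.** The strongest counter-argument is that such events may be very rare. Section 2.3 excludes NYHA class III–IV, unstable cardiac disease, disabling orthopaedic disease and contraindications to exercise. Section 2.4.1 describes a one-week programme with individualised intensity and heart-rate monitoring. This stands: the size cannot be established from the article, and the 1% row belongs in the range.

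Some stronger readings are tempting but not supported:

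- *The rule removes the arm's worst outcomes.* The only example is a fall, with no severity threshold and no outcome data. Poorer walking among those removed is plausible but inferred.
- *The rule hides harms.* Nothing says that adverse events or reasons for withdrawal go unreported. Section 2.8 takes ICU stay and postoperative recovery data from electronic records, so withdrawal need not mean losing those data.
- *Rule (3) adds to the same bias.* It can apply in either arm, and that referral depends on how the patient fared is speculation.
- *Section 2.9 treats these withdrawals as ordinary attrition.* It does not say what counts as attrition or how withdrawn patients are handled.

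It can also be said that analysis sets belong to an analysis plan that is not shown. That is fair for the analysis set and any sensitivity analysis. It does not answer the main point: rule (2) is a conduct rule that this article states, and it governs whether assessments are made at all.

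**Conclusion.** The concern holds for rule (2). As written, it takes patients out of the trial after randomisation, in one arm only, for a reason linked to treatment and plausibly to walking ability. Nothing in the article keeps them in follow-up. The likely direction favours prehabilitation.

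The size is unknown. The illustrated inflation runs from 0.5 m to 10 m against the 20 m target. It rests on an assumed 1–10% of the arm being removed and an assumed deficit of 50–100 m, and on withdrawn patients contributing no T2 value. The case for correction does not depend on the upper end of that range: the asymmetry is built into the rule, and the missing walks cannot be recovered after the trial.

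**What to change.** In section 2.3, reword rule (2) so that stopping the programme and leaving the trial are separate events. When the programme stops is left as the protocol has it. Then state that:

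- T1–T3 assessments continue where feasible, and record-based outcomes continue to be collected, unless the patient withdraws consent
- these patients are analysed in their assigned arm (a cross-reference suffices if the analysis plan already says so)
- these events are reported by arm

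As a secondary suggestion, patients meeting rule (3) could also be kept in follow-up in both arms. That is not part of the one-sided bias.

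The cost is a short change of wording and a few extra assessments. Some of these may fall off schedule if an event postpones surgery, because T2 and T3 are timed relative to it.
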